Motivation and external engagement also are important for Internet-based prevention programs. The literature indicates that adolescents need to be reminded and encouraged to visit intervention websites to sustain use [41,42]. Many effective Internet-based programs for adults use some form of reminder or professional guidance to encourage engagement, and similar protocols also have been effective in adolescent Internet prevention programs [33,37-39]. Recent studies also indicate that motivational interviews with participants linking personal goals to intervention use are more effective at maintaining site use and achieving preventive effects than just brief advice and reminders alone [33].

Cognizant of this research on Internet-based prevention, we developed CATCH-IT (Competent Adulthood Transition with Cognitive Behavioral Humanistic and Interpersonal Training) [43-49] a public health, primary care/Internet-based depression prevention program for adolescents. CATCH-IT teaches resiliency skills to at-risk adolescents through teen-friendly, interactive web-based modules, and incorporates both motivational support by primary care professionals and an Internet-based parental behavioral change course. CATCH-IT targets multiple etiological elements by teaching skills from empirically supported, face-to-face interventions (including Cognitive Behavioral Therapy (CBT), Interpersonal Psychotherapy (IPT), and Behavioral Activation (BA); [33,45,46]), and employs a multi-channel learning process with culturally relevant lessons, stories, and graphics to increase personal relevance and multi-modal learning opportunities. Should this intervention prove efficacious, the public would have the first effective, low-cost, and acceptable depression prevention intervention offered through primary care for young people that would be free to users and available universally, without further burdening the mental health care delivery system or creating any new care delivery infrastructure.

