### Primary care site recruitment and implementation process

The primary care aspects of the study (including recruitment, provider motivational interview, and referrals to treatment, when clinically indicated) are centered in pediatric clinics in urban and suburban areas in both Chicago, IL and Boston, MA. Practices are recruited either by study staff or by health care providers at existing study sites. Healthcare providers (physicians and nurse practitioners) and office nursing staff (for example, registered nurses and medical assistants) are informed about the study and provide written consent to participate in specific roles described below. Each participating healthcare provider also completes pre- and postquestionnaires regarding the intervention, status of the clinic, and their experiences in participation. At each site, a research coordinator or study champion is identified to communicate with study staff about room scheduling, weekly recruitment times, positive and negative screens, and other study details. Providers and other medical professionals are instructed in the screening protocol. Office nursing staff conduct the screenings of the adolescents with the two question screening tool. Health care providers are trained in Motivational Interviewing either with a one hour program using a lecture/discussion format and example video tapes, a three-session training, or through more informal interactions with the study staff, using detailed scripts. Providers receive semi-structured feedback on their motivational interview technique after completing 1 to 2 interviews with teen participants at their clinic. Each motivational interview takes approximately 10 minutes to complete. Three interviews are completed over the course of the year with each participant, with each provider interviewing one to eight patients. Study-employed mental health professionals, who conduct three motivational phone calls with the participants during the intervention, are also trained in Motivational Interviewing. Throughout the study, study staff members are in frequent contact with the primary care clinics, discussing logistical details, reporting when screened adolescents require referral to treatment, and providing feedback about the clinic’s participation.

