### The CATCH-IT intervention

The CATCH-IT intervention has an Internet component (with separate adolescent (14 modules) and parent (4 modules) programs) and a motivational component (three primary care physician motivational interviews at time 0, 2 months and 12 months, and one to three study-staff coaching phone calls either at 1 month (Chicago) or at 2 and 4 weeks and 18 months (Boston)). In addition to the motivational interviews and coaching phone calls, three “check-in” calls during weeks 1 to 3 are offered to participants; these calls are intended to ensure participants have access to the Internet and take approximately five minutes to complete.

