### CATCH-IT: The parent internet component

The parent Internet component of the intervention is based on an adaptation of [name] and [name]’s clinician-facilitated and lecture intervention approaches from the Preventive Intervention Project [43]. This intervention helps parents develop the awareness and skills needed to help build resiliency in their children. The intervention also seeks to reduce known risk factors for adolescent depression. To address the key mediating role of parental depressed mood, a personalized component is available to parents with depressed mood. A paper and pen version of the parent component was originally piloted during the phase 2 CATCH-IT clinical trial, but parents strongly requested their own Internet site. A paper version of the current parent program is available in Spanish.

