#### Mediator analysis

In addition to examination of whether the intervention impact varies as a function of baseline symptoms, we will evaluate potential mediators including change in adolescent motivation, principles (intervention experience characteristics) of effective preventive interventions (adherence/dose, positive relationships, training and socio-cultural relevance, as reported by the adolescent) and changes in adolescent vulnerability and protective factors (social support, automatic negative thoughts, depressed mood). Based on our recent work on a comparison of analytic models for mediation with nonlinear models [113], we will use the “product of coefficients” method to conduct tests of mediation and the bootstrap method for accurate confidence intervals [114]. To examine the effects of adolescent participation with the website, we will conduct complier average causal effect (CACE) analyses that include covariates predicting participation status [115-118].

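### The planned CACE analysis cannot isolate the effect of website participation, because assignment to CATCH-IT also brings provider interviews, coaching calls and a parent programme that do not depend on the adolescent using the site.

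*Protocol article*

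**What the plan says.** The Mediator analysis section of the protocol article names both a target and a method. The target is given by "To examine the effects of adolescent participation with the website". The method follows in the same sentence: "we will conduct complier average causal effect (CACE) analyses that include covariates predicting participation status". The text does not say whether the exclusion restriction is imposed.

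CATCH-IT has several components besides the adolescent site:

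- **Provider interviews.** The CATCH-IT intervention section lists "three primary care physician motivational interviews at time 0, 2 months and 12 months". The section on primary care site recruitment adds: "Three interviews are completed over the course of the year with each participant".
- **Coaching calls.** One to three calls are made by study staff, on schedules that differ between Chicago and Boston.
- **Check-in calls.** Three "calls during weeks 1 to 3 are offered to participants", to make sure that they have Internet access.
- **Parent programme.** There are four modules and an optional fifth, largely about depression and resilience. Of this programme the article says: "This intervention helps parents develop the awareness and skills needed to help build resiliency in their children".

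The Background section presents these as part of the intervention, which "incorporates both motivational support by primary care professionals and an Internet-based parental behavioral change course". The section on the motivational component gives it the purpose of lowering vulnerability and strengthening protective factors, as well as promoting use of the programme.

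For the Health Education arm, the article describes routine provider contact and a parent site on general adolescent health. It describes no motivational interviews or coaching calls in that arm.

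**The concern.** A CACE compares outcomes by assignment among those who would take up a named exposure. It can be read as the effect of that exposure only if assignment changes nothing else that matters for the outcome. Here the named exposure is site participation, but assignment changes several other things. The first provider interview is at time 0, so it does not wait for any site use, and the parent programme works through the parent. Covariates that predict participation help to identify who would participate. They do not remove the effect of the other components.

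Aim (d) of the study is to learn for whom and how the programme works. If the CACE is reported as the effect of website participation, part of what human contact and the parent course achieve may be counted as a website effect.

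**Working it through.** The article gives no CACE estimate or uptake rate, so there is no stated figure to reproduce. The check is algebraic, with the planning assumptions used only to set a scale.

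**Notation and assumptions.** Let p be the share of CATCH-IT adolescents who use the site, W the website effect in users, and M the effect of the other components. M is taken as equal in users and non-users. Effects add on the risk-difference scale, and controls have no access to the CATCH-IT site.

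**Step 1: ITT effect.** Users gain W + M and non-users gain M, so ITT = p(W + M) + (1 - p)M = pW + M.

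**Step 2: CACE under the exclusion restriction.** The effect in non-users is set to zero, so CACE = ITT/p = W + M/p. The excess over W is M/p, which grows as uptake falls.

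**Step 3: CACE without the restriction.** If the model identifies it correctly, the complier effect is W + M, because users also receive the other components. The excess over W is M.

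**Step 4: scale.** The Sample size analysis section assumes 72% of controls free of depression at one year, an exponential rate through year two, and a hazard ratio of 0.62.

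- Control 2-year risk: 1 - 0.72^2 = 0.482
- CATCH-IT 2-year risk: 1 - 0.72^(2 × 0.62) = 0.335
- Planned ITT risk difference: 0.482 - 0.335 = 0.147

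These inputs are usable. With the stated attrition and 200 per arm they give about 132 events and 78.4% power (Schoenfeld formula, two-sided 0.05 assumed), close to the stated 80%.

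**Step 5: illustration.** Both p and M are assumed. At p = 0.5 and M = 25% of ITT:

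- M = 0.25 × 0.147 = 0.037
- W = (ITT - M)/p = 0.75 × 0.147/0.5 = 0.221
- CACE with the restriction = 0.147/0.5 = 0.294
- CACE without it = 0.221 + 0.037 = 0.257 (from unrounded values)

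| p | M as share of ITT | CACE with restriction | CACE without | Website effect W |
|---|---|---|---|---|
| 0.5 | 0 | 0.294 | 0.294 | 0.294 |
| 0.5 | 25% | 0.294 | 0.257 | 0.221 |
| 0.5 | 50% | 0.294 | 0.221 | 0.147 |
| 0.7 | 25% | 0.210 | 0.194 | 0.158 |
| 0.7 | 50% | 0.210 | 0.179 | 0.105 |
| 0.9 | 25% | 0.163 | 0.159 | 0.123 |
| 0.9 | 50% | 0.163 | 0.155 | 0.082 |

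With the restriction, the ratio of CACE to W is 1/(1 - share): 1.33 at 25% and 2 at 50%, whatever the uptake.

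**Step 6: limits of the scale.** At p = 0.3, ITT/p = 0.490, which exceeds the control risk of 0.482. If users and non-users have equal control risk, complete prevention in every user would still leave 0.7 × 0.482 = 0.337, above the planned 0.335. The planned effect and the exclusion restriction are therefore incompatible at that uptake. The same decomposition should not be done on the log-hazard scale: risks average over users and non-users, but log hazards do not.

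**The case against.** The strongest reply is that the article does not specify the estimator. It states no exclusion restriction and no division by the uptake rate, and model-based CACE with covariates can be fitted with or without the restriction. A reader might infer that the plan credits the website with the whole effect of assignment. The documents do not establish that; it would be so only under the restriction. The point does not depend on it, because without the restriction the complier effect is still that of the package in users.

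A second reply is that several components mainly promote engagement. Check-in calls concern access, coaching calls largely encourage completion, and the interview weighs the pros and cons of taking part. Effects that run through site use respect the restriction. This stands for the check-in calls and partly for the others. It does not cover the parent programme or the wider purpose stated for the motivational component.

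Third, the direction of the bias is not proven. Both pilot arms had the Internet programme, so the pilot's advantage for motivational interviews may have come through greater site use. If M were harmful, at -25% of ITT and p = 0.5, the restricted CACE of 0.294 would understate a website effect of 0.368. Nor does the article show that non-users actually receive every component: check-in calls are only offered, and 186 parents are enrolled against 234 adolescents.

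Finally, a reader might infer that the analysis would support offering the website alone. The Discussion instead presents CATCH-IT as computer-based instruction blended with human contact, so that inference is not supported.

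**Conclusion.** The concern holds in this form: neither version of CACE delivers the quantity that the sentence names. With the restriction the result differs from the website effect by M/p, and without it by M. Both versions exceed the website effect if the other components are beneficial on balance. The protocol presumes that benefit but does not demonstrate it. A categorical statement that the analysis overstates the website effect would go further than the documents allow.

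The size is unknown, because p and M are not given. In the illustrations with p from 0.5 to 0.9 and M at 25% to 50% of ITT, the restricted CACE is 1.33 to 2 times the website effect. If M is zero there is no bias. These figures rest on additive risk differences and on M being equal in users and non-users. The consequence is confined to a supplementary analysis serving aim (d).

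**What to change.** Make three changes to the Mediator analysis text:

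1. Describe the CACE as the effect of the CATCH-IT package among adolescents who would use the site, not as the effect of website participation.
2. State whether the exclusion restriction is imposed.
3. Add a sensitivity table, labelled exploratory, that allows a non-zero effect M of assignment in non-users (for example 0 to 50% of ITT). Show the implied website effect, (ITT - M)/p, on the risk scale.

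Widening the complier class to adolescents who received any CATCH-IT component would not help. Interviews start at time 0 and are planned with each participant, so nearly everyone would be a complier and the CACE would reduce to the ITT effect.

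The cost is some rewording and a modest amount of extra analysis from site logs already planned under Adherence and log files. The website-specific estimate becomes less precise. Trial conduct and the primary comparison do not change.

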#### Moderator analysis

We expect to conduct tests of moderation in eight domains: (a) adolescent demographic and cultural factors [119-121], (b) adolescent vulnerability factors and adverse events [51], (c) adolescent motivation and attitudes [62], (d) adolescent relationship with the provider, (e) parent and child comorbid psychopathology, (f) adolescent treatment before and during the study [122,123], (g) level of adolescent adherence/participation, and (h) study site. We will use subgroup analyses and tests of interaction to evaluate moderator effects. We anticipate conducting several different subgroup analyses including the following: (a) adolescent ethnicity, sex and age; (b) neighborhood socioeconomic level; (c) adolescent level of risk, including risk stratified by varying levels of vulnerability from different sources (for example, family, cognitive or social risk); and (d) practice factors (provider motivational interview quality, practice type).

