### Control group: health education

Health Education (HE) is an attentional control. This Internet site comprises 14 modules, 13 of which provide instruction on nutrition, safety, and other teen health and wellness topics. The 14th module discusses mood and seeking mental health treatment, and also addresses stigma and negative attitudes toward the treatment of mental disorders, as these have previously been identified as barriers to seeking and adhering to treatment [47,67]. Module 14 does not provide instruction in Behavioral Activation, Cognitive Behavioral Therapy, or Interpersonal Therapy. The HE Internet site does not include interactive elements such as videos, question prompts, or feedback on mood or progress.

The HE components are similar to those employed in previous primary care-based quality improvement/Chronic Care Model Interventions, incorporating patient psychoeducation, active monitoring and referral, with routine contact with a primary care provider. The HE group receives the same assessments as the CATCH-IT group (including notification and referral to mental health services) and routine contact with their primary care provider (PCP; estimated two to three visits per year), and also incorporates a parent Internet program that provides similar psychoeductional content about general adolescent health. Psychoeducation Internet site use is monitored to compare with use of the CATCH-IT intervention as an attentional control. Self-harm risk is managed based on a standard protocol.

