##### Physician Relationship Scale

The Physician Relationship Scale [33] contains nine items rating the participant’s relationship with his/her provider in understanding, engagement, helpfulness, comfort, and trust. Only adolescents in the CATCH-IT condition are administered this measure. This self-report measure is rated on a five-point Likert scale (1 = *strongly disagree* to 5 = *strongly agree*). A sample item is, “I trust my physician.” Higher scores reflect a more positive relationship with the provider. In our pilot study, Cronbach alpha was .85 [5,33].

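### Two planned moderators arise after randomisation, and a third, the provider relationship, rests on a scale given only to the CATCH-IT arm

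*Protocol article*

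**What the plan says.** The Moderator analysis section names eight domains. Three matter here: "d) adolescent relationship with the provider", and "f) adolescent treatment before and during the study [122,123], (g) level of adolescent adherence/participation". The method is fixed in one sentence, without restriction to baseline values: "We will use subgroup analyses and tests of interaction to evaluate moderator effects". The subgroup list that follows includes "practice factors (provider motivational interview quality, practice type".

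Four other places bear on these items.

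- **Physician Relationship Scale (Instruments):** "Only adolescents in the CATCH-IT condition are administered this measure". No other instrument in the article is described as measuring the relationship with the provider.
- **The CATCH-IT intervention:** this arm contains "a motivational component (three primary care physician motivational interviews at time 0, 2 months and 12 months".
- **Control group: health education (HE):** HE has "routine contact with their primary care provider (PCP; estimated two to three visits per year". No motivational interview is described. HE site use is monitored for comparison with CATCH-IT.
- **Mediator analysis:** adherence or dose is listed as a potential mediator, together with "positive relationships, training and socio-cultural relevance, as reported by the adolescent". The same section plans a CACE analysis of website participation, with covariates that predict participation.

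**The concern.** A test of effect modification asks whether the effect of assignment differs between kinds of participant. Randomisation makes the arms comparable within a kind only if the kind is settled before assignment. If assignment can influence who falls into a subgroup, the CATCH-IT and HE members of that subgroup are different sorts of people, and their difference mixes selection with effect.

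Both quoted variables are open to this. How much a participant uses a site can depend on which site was assigned: HE has no videos, question prompts or feedback. Treatment during the study can follow from the outcome, because participants in both arms are assessed and referred when a problem is found. The plan itself treats adherence as a consequence of assignment in the Mediator analysis section and as an effect modifier in the next.

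The provider-relationship domain has a simpler problem. An arm-by-moderator interaction needs moderator values in both arms, and HE has none on this scale.

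At stake is aim (d), for whom and how the programme works. A reader of the results could not tell a differential effect from a selection artefact.

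**Working it through.** The plan states no figure for the moderator tests, so there is none to reproduce. Its 80% power refers to the main survival comparison. The check has two parts.

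**1. Provider relationship: can the interaction be estimated?**

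Take the model with columns [1, A, M, A×M], where A is arm (1 = CATCH-IT, 0 = HE) and M is the scale score. M is seen only when A = 1. Dropping HE leaves A constant at 1, so A×M = M. Keeping HE with any constant filled in, say 0, again gives A×M = M in every row. With 200 per arm the matrix has rank 3, not 4. The scale's slope within CATCH-IT can be estimated; its difference from the HE slope cannot.

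**2. Post-randomisation moderators: what happens when there is no effect?**

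*Site use.* From the plan: one-year control event-free proportion 72%, so the baseline yearly hazard is −ln(0.72) = 0.329. Assumed: an unmeasured trait U ~ N(0,1) multiplies the hazard by exp(−0.4U), or 0.67 per SD; a participant is a high user when U plus standard normal noise exceeds a threshold; there is no arm effect in anyone. Within each use level, HR = ln(1 − risk in CATCH-IT) / ln(1 − risk in HE) at one year, from 4 million simulated participants. The overall HR is 1.00 in every scenario.

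| Assumed link of use to arm and prognosis | High use, CATCH-IT / HE | HR, high users | HR, low users |
|---|---|---|---|
| Same link to U in both arms, lower use in CATCH-IT | 36% / 64% | 0.88 | 0.88 |
| Same link, equal use | 50% / 50% | 1.00 | 1.00 |
| Same link, higher use in CATCH-IT | 64% / 36% | 1.14 | 1.13 |
| Use tied to U in CATCH-IT only, equal use | 50% / 50% | 0.79 | 1.23 |

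For the last row, one-year risks among high users are 23.9% (CATCH-IT) and 29.2% (HE): ln(0.761)/ln(0.708) = 0.273/0.345 = 0.79. Among low users they are 34.6% and 29.2%: ln(0.654)/ln(0.708) = 0.425/0.345 = 1.23.

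*Interaction tests at the trial's size.* Assumed: 400 participants, 2,000 runs, a continuous outcome with SD about 1 (higher is worse), no arm effect, nominal 5% test.

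| Moderator | False-positive interactions | Spurious arm difference by level |
|---|---|---|
| Baseline variable | 5.2% | about 0 and 0 |
| Adherence tied to prognosis in CATCH-IT only | 98.7% | +0.39 (non-adherent), −0.40 (adherent) |
| Treatment during study, following symptoms, higher threshold in CATCH-IT | 5.6% | +0.22 (untreated), +0.27 (treated) |

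The last row shows why a clean interaction test is no reassurance: the interaction is near its nominal rate, yet both subgroup contrasts are wrong. The baseline moderator behaves as it should.

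**The case against.** Much of the case on the other side stands.

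**Size and direction.** A reader might infer that the likely product is a false finding that the programme works in those who use it. The documents do not support that. It appears only if use tracks prognosis differently in the two arms. With the same link in both arms and unequal use, the hazard ratio is shifted about equally in both strata and the interaction test shows almost nothing; with equal use there is no bias. The article gives neither use rates by arm nor the relation of use to prognosis.

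**Interview quality.** A reader might also infer that it cannot be tested because HE has no interviews. But the plan lists it under practice factors, randomisation was blocked by practice, and each provider interviews one to eight patients. A provider- or practice-level score could be assigned to both arms. Only a patient-level value lacks an HE counterpart.

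**Mediation.** It is tempting to say that the positive-relationships mediator also fails. The article does not say which instrument measures it, and only one of the five in the Relationships group is restricted to CATCH-IT. Nor does it restrict the module-experience ratings to one arm.

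**Already handled.** CACE is planned for participation, and HE use is logged, so the adherence interaction can be computed. That is true, but the Moderator analysis section still keeps adherence as a conventional moderator.

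**Condensed article.** Baseline definitions are commonly left to the analysis plan. That covers several domains, but not the explicit inclusion of treatment during the study, and an analysis plan cannot supply scale values that were not collected. The general remark that HE receives the same assessments gives way to the specific restriction on the provider scale.

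**Conclusion.** The concern holds in this form. Treatment during the study and adherence or participation are post-randomisation variables, and the planned subgroup and interaction tests on them can be biased in either direction. In the illustrations the null hazard ratio of 1.00 moved to anything from 0.79 to 1.23 within strata. Those sizes rest entirely on assumed links between use, arm and prognosis. What is general is the loss of protection by randomisation, not the magnitude or the sign.

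The provider-relationship interaction is not estimable with the scale as administered; this needs no assumption beyond its being the only instrument for that domain. If the same scale also serves as the positive-relationships mediator, its arm-to-mediator coefficient is likewise not estimable, but that remains conditional. Interview quality is usable as a moderator only above patient level. The treatment-before-study part of domain (f) is sound.

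These are secondary analyses under the last of four aims. The primary intention-to-treat comparison is untouched.

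**What to change.** Amend the Moderator analysis wording as follows.

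1. Limit moderator tests to baseline variables measured in both arms.
2. Reduce domain (f) to treatment before the study. Report treatment during the study as an outcome by arm; the Child and Adolescent Service Assessment (CASA) is collected at baseline and all follow-ups.
3. Drop domain (g) as a moderator and answer the participation question with the CACE analysis already planned.
4. Report the Physician Relationship Scale as a descriptive predictor within CATCH-IT, not as a moderator.
5. Define interview quality at provider or practice level and apply it to both arms, or else report it within CATCH-IT only.

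The cost is wording and fewer moderator domains. Giving the provider scale to HE participants is not needed for this fix. With 234 of 400 enrolled, 166 remained, or about 83 in HE, so it would be a mid-trial change in data collection with partial coverage. The article also does not say when CATCH-IT participants complete the scale, so baseline values in HE might not match those already collected.
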